
#### Personality measures

##### NEO-five factor Inventory

The NEO FFI is the short version of the NEO-PI-R [88], designed to assess the five personality dimensions through 60 items. In this study, only the subscales of neuroticism and extraversion are used. Each scale contained 12 items with a five-point Likert response format. Two-week retest reliability is uniformly high, ranging from 0.86 to 0.90 for the five scales [89], and internal consistency ranges from 0.68 to 0.86 [89].The Spanish version of the NEO FFI has been found to be good [90].

#### Quality of life

*EuroQol 5D* (EQ-5D-Spanish version) [91] is a generic instrument for measuring health-related quality of life. It can be used in relatively healthy individuals (general population) as well as in groups of patients with different pathologies. Each individual rates his/her own health on each of the two parts of the questionnaire. In the first part, the individual must check the level corresponding to his/her state of health in each of the five domains: mobility, self-care, daily activities, pain/discomfort and anxiety/depression. Each dimension is divided into three levels of severity (without problems, some problems or moderate problems, and severe problems), yielding a population-based preference score or societal index (SI). There are 243 possible combinations - health states -, and the SI is calculated on the basis of these health states. The index value ranges from 1 (best health state) to 0 (death), although there are negative values for the index corresponding to those health states that are rated as worse than death. In the second part of the questionnaire, the individual values his/her own health on a more general visual analogical scale (VAS), a 10 cm vertical line on which the best and worst imaginable health states score 100 and 0, respectively.

#### Suicidal ideation

A suicide item has been included within the ODSIS [92] with the aim of obtaining a suicide risk indicator throughout the treatment. The total score depends on this single item, and the maximum score is 4, with a range from 0 (“*absence of thoughts of suicide*”) to 4 ("*thoughts of suicide all the time*").

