### Ethics

The study follows the guidelines of the Declaration Helsinki and existing guidelines in Spain and the European Union for the protection of patients in clinical trials. As noted, all participants will be volunteers, and they will sign the online informed consent to form part of the study once it has been explained to them. Participants will have the possibility of withdrawing from the study at any time. The recruitment of participants will be carried out by qualified personnel from a clinical point of view. Participants allocated to the *WL* condition will be offered the opportunity to receive the *TIBP* or the *TIBP + PA* intervention after the waiting time has ended. Based on the literature, no special difficulties are expected. However, any undesired event would not only mean the participant’s departure from the trial, but s/he would also be offered the possibility of receiving psychological care at the Emotional Disorder Clinic in Universitat Jaume I, or of being referred if his/her medical condition required it.

A fundamental aspect in a project of this nature is data protection. To protect information, strategies using personal passwords and data via AES encryption (AES-256; Advanced Encryption Standard) will be used. Personal data will be replaced by codes and data, which must be collected by clinicians (e.g. age, sex, address, and phone), stored separately from other data, and only made available to researchers responsible for the study, always protecting the right to privacy.

The study has been approved by the Ethics Committee of Universitat Jaume I (Castellón, Spain). The trial was registered at clinicalstrial.gov as NCT02578758.

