### Adaptation to the web

This protocol has been adapted to a multimedia web platform (video, images, etc.) and can be applied over the Internet (https://www.psicologiaytecnologia.com/). It is developed for optimal use on a PC or a tablet, and it allows individuals to do the modules from their home and at their own pace. The ease of use of the program has been strengthened because it presents a streamlined navigation, which allows users with less experience in handling new technologies to know where they are and how to keep moving forward at any time. The web adaptation of the protocol is the same in both conditions (TIBP and TIBP + PA), with the only difference being the inclusion or not of the modules that contain the PA-regulation component.

Duration of the program can vary among users, and participants in both treatment conditions have access to the protocol for a maximum period of 18 weeks. The program recommends working on one module for at least one entire week, and it sends messages encouraging the patient to continue to work to benefit from it. In both conditions, the modules include exercises and tasks to practice each technique and skill. Moreover, the platform is ready to welcome all participants with information about the treatment and its objectives, as well as general information and recommendations about how to benefit from it.

Regarding the assessment of patients within the program, after the “Welcome”, initial online questionnaires are presented as the pre-treatment assessment. In addition, post-module brief questionnaires to evaluate anxiety, depression, and positive/negative affect (OASIS, ODSIS, PANAS) are also filled out throughout the program. A noteworthy aspect of the program is that it allows the therapist to have access to all this information and receive an alert if the patient’s condition worsens. The program includes suicide risk alarms that consist of an email to the clinical team with information about a high risk of suicide. These alarms are generated when the system detects that the participant rated high on the suicidal ideation items. It allows the clinician to contact the patient and evaluate the actions that should be taken to protect him/her. Finally, after the treatment, the participants complete the online assessment in the post- and follow-up periods.

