#### Post-module measures

Scores on anxious and depressive symptomatology will also be obtained after each module has been completed.

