#### Expectation of treatment scale and opinion of treatment scale.

The Expectation of Treatment Scale and Opinion of Treatment Scale are questionnaires adapted from Borkovec and Nau [96]. Each scale contains five items, rated from 0 (“strongly disagree”) to 10 (“strongly agree”), which cover how logical the treatment seemed, to what extent it could satisfy the patient, whether it could be used to treat other psychological problems, and its usefulness for the patient’s specific problem. The expectation scale is applied once the intervention has been explained, at the end of the “Welcome module”. This scale measures the patient’s subjective expectations about the treatment. In addition, the opinion scale is administered when the patient has completed the treatment, and its aim is to assess satisfaction with the intervention. Our group has used this questionnaire in several research studies [48, 97].

The study measures and assessment times are summarized in Table 2.

**Table 2 Tab2:** Study measures and assessment times

Measure	Aim	Time of assessment
MINI Neuropsychiatric Interview	Diagnosis	BL, Post-T and FU
PANAS	Positive and negative affect	Post-T and Post-module
BDI-II	Severity of depression	BL, Post-T and FU
BAI	Severity of anxiety	BL, Post-T and FU
OCI-R	Severity of OCD symptoms	BL, Post-T and FU
PDSS-SR	Severity of PD and agoraphobia symptoms	BL, Post-T and FU
PSWQ	Severity of GAD symptoms	BL, Post-T and FU
SIAS	Severity of SAD symptoms	BL, Post-T and FU
NEO FFI	Neuroticism and Extraversion	BL, Post-T and FU
EQ-5D	Health-related quality of life	BL, Post-T and FU
OASIS	Severity of anxiety	Post-module
ODSIS	Severity of depression	Post-module
Suicide item	Suicidal ideation	BL, Post-module, Post-T and FU
Expectation of Treatment Scale	Expectation of treatment	BL
Opinion of Treatment Scale	Opinion of treatment	Post-T

*BL*, Baseline; *Post-T*, post-treatment; *FU*, follow-ups, 3 and 12-month follow-ups; *PANAS*, Positive and Negative Affect Scale; *BDI-II*, Beck Depression Inventory-II; *BAI*, Beck Anxiety Inventory; *OCI-R*, Obsessive-Compulsive Inventory-Revised; *PDSS-SR*, Self-Reported Panic Disorder Severity Scale; *PSWQ*, Penn State Worry Questionnaire; *SIAS*, Social Interaction Anxiety Scale; *NEO FFI*, NEO-Five Factor Inventory; *EQ-5D*, EuroQoL-5D questionnaire; *OASIS*, Overall Anxiety Severity and Impairment Scale; *ODSIS*, Overall Depression Severity and Impairment Scale

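### The waiting-list arm (69 of 207) has no scheduled suicide-item reading between baseline and post-treatment, because the only intermediate timing depends on completing treatment modules

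*Protocol article*

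**What the plan says.** All references are to the protocol article.

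- **Purpose of the item** (Suicidal ideation): "A suicide item has been included within the ODSIS [92] with the aim of obtaining a suicide risk indicator throughout the treatment". It is a single item scored 0 to 4.
- **Timing** (Table 2, suicide item row): "BL, Post-module, Post-T and FU". The text introduces the table with "The study measures and assessment times are summarized in Table 2". The table is not split by arm.
- **What post-module means** (Post-module measures): "Scores on anxious and depressive symptomatology will also be obtained after each module has been completed".
- **Alarm** (Adaptation to the web): "The program includes suicide risk alarms that consist of an email to the clinical team with information about a high risk of suicide". Its trigger is also given: "These alarms are generated when the system detects that the participant rated high on the suicidal ideation items". The response follows: "It allows the clinician to contact the patient and evaluate the actions that should be taken to protect him/her".
- **Waiting-list access to the program** (Ethics): these participants are offered either "intervention after the waiting time has ended".
- **Contact between assessments** (Support): weekly calls of at most 5 minutes, two text messages a week, and automatic e-mails after 15 days without access. All of this is described for the two treatment conditions.
- **Other safeguards**: Table 1 excludes people at high suicide risk. Under Ethics, an undesired event leads to leaving the trial, with an offer of clinic care or referral.

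**The concern.** The monitoring follows completed modules, not time at risk. A participant who has no modules generates no post-module reading, and without a rating the alarm has nothing to act on. The arm without treatment is therefore also the arm without interim monitoring.

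What is at stake is patient safety. The trial enrols people with diagnosed emotional disorders, major depression included, and the Introduction says it aims to reach people outside primary or specialized care. Table 1 also rules out other psychological treatment during the study. A therapist elsewhere is thus unlikely to notice a waiting-list participant getting worse, although some participants on stable medication may see a prescriber. The sponsor judged an interim risk indicator worth having in the treated arms, and the article gives no reason for leaving it out of the untreated one.

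**Working it through.** **Step 1. Size of the arm.** Sample size states 207 participants, 69 per group.
- With a three-group one-way ANOVA, f = 0.25 and alpha 0.05, power is 0.797 at N = 156 and 0.805 at N = 159. The article's 159 (53 per group) is reproduced.
- 159 × 1.30 = 206.7, rounded up to 207. The article's total is reproduced.
- 207 / 3 = 69, and 69 / 207 = 33.3%.

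(Dividing by 0.70 instead would give 228, or 76 per group. That is a separate matter, and the waiting list would still be one third.)

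**Step 2. Scheduled suicide-item readings after baseline and before post-treatment.** Post-module is the only such timing in Table 2.

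| Arm | Modules before Post-T | Interim readings |
|---|---|---|
| TIBP | 12 | up to 12 |
| TIBP + PA | 16 | up to 16 |
| Waiting list | 0 | 0 |

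The zero follows from two statements taken together: post-module scores need a completed module, and the waiting list gets the program only once the wait is over.

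**Step 3. Does anything else cover the wait?**
- *Alarm*: a feature of the program, triggered by a high rating. No rating is scheduled during the wait.
- *Calls, texts and reminder e-mails*: described for the two treatment conditions only.
- *Exclusion of high suicide risk*: screens at entry and does not detect later onset.
- *Offer of care or referral*: acts once an undesired event is known.
- *Post-treatment assessment*: suicide item, MINI and BDI-II. This can pick up ideation still present at the end of the wait, but not before.

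**Step 4. Length of the gap and effect of an added item.** The article does not state how long the wait lasts. I assume a range from 12 weeks (twelve TIBP modules at one a week) to 18 weeks (maximum program access). With an item every 4 weeks, as an example:
- 12-week wait: weeks 4 and 8, so 2 readings per person; 69 × 2 = 138 in the arm.
- 18-week wait: weeks 4, 8, 12 and 16, so 4 readings per person; 69 × 4 = 276 in the arm.
- The longest scheduled gap falls from the whole wait (12 to 18 weeks) to 4 weeks.

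The article gives no rate of suicidal ideation, so the number of cases that would be found earlier cannot be estimated.

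**The case against.** **The article is condensed.** Table 2 is a summary not split by arm, the length of the wait is missing, and ethics approval is reported. A waiting-list safety procedure may well sit in the full protocol or the ethics file. This stands in part: nobody can conclude from the article that no such procedure exists. But the article does not leave the topic to another document. It sets the item's timings, its purpose and the alarm, and ties each to treatment. Followed as written, these leave the wait uncovered.

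**Nothing is misstated.** The stated aim is an indicator during treatment, and the schedule delivers that. True. The point is about the reach of the chosen design and not about an internal contradiction.

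**The alarm may reach further than the modules.** Its trigger is worded as items in the plural, in a section that also covers the online baseline and post-treatment questionnaires. It may therefore apply to waiting-list assessments at those times. Even so, it would add nothing between them.

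**A reader might infer that treated participants who stall are equally exposed.** It is true that they give no post-module reading until the next module is completed. But the Support section gives every treated participant a weekly call, two texts a week and an e-mail after 15 days without access. The calls are brief and are not described as suicide checks, yet they are regular human contact that the waiting list is not described as having. The documents do not support extending the point to the treated arms.

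**Monitoring has a cost to the comparison.** Under Ethics an undesired event ends participation. If an alarm during the wait were handled that way, the added item would create withdrawals in the control arm. This objection stands, and the fix has to deal with it.

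**Conclusion.** The point holds for the waiting list. As scheduled, 69 of 207 participants (33.3%) have no suicide-item reading between baseline and post-treatment, against up to 12 and up to 16 readings in the treated arms. Neither the alarm nor the support calls, as described, fill the gap.

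This rests on two readings: that Table 2's row applies to the waiting list except where a module is needed, and that Post-T for this arm falls at the end of the wait. The 12 to 18 weeks is my assumption.

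Two further inferences would go too far. A reader might conclude that suicidal ideation in this arm is never detected; the post-treatment suicide item, MINI and BDI-II rule that out, so the problem is delay. A reader might also conclude that the trial's efficacy results are compromised; the gap touches neither the primary outcomes nor their analysis. It is a low-cost safety improvement, held with medium confidence because a fuller protocol could already provide for it.

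**What to change.** 1. **Table 2**: for the waiting-list arm, add the single suicide item online at fixed dates during the wait. The clinical team should set the interval; every 4 weeks is only an example. Keep all existing timings.
2. **Suicidal ideation**: extend the stated purpose to *throughout the treatment or waiting period*.
3. **Adaptation to the web**: state that the existing email alarm and clinician response also apply to these readings.
4. **Ethics**: state that an alarm alone is not an undesired event that ends participation, and that anyone who needs care is referred but still assessed at post-treatment.

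**Cost.** Table 1 already requires home Internet and an e-mail address, so no new channel is needed. The burden is 2 to 4 one-item contacts per waiting-list participant under the assumed 12 to 18 weeks and a 4-week interval. The downsides are slight measurement reactivity, clinician time to answer alarms, and possibly some control participants referred to care, which would make the waiting list a little less untreated. Item 4 keeps their post-treatment data in the intention-to-treat analysis.

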#### Post-module measures

Scores on anxious and depressive symptomatology will also be obtained after each module has been completed.

##### *Overall Anxiety Severity and Impairment Scale (OASIS)* [93]

The OASIS consists of a 5-item questionnaire with a scale from 0 to 4, which measures the frequency and severity of anxiety, as well as the level of avoidance, work/academic/home interference, and social and everyday life impairment related to anxiety symptoms. The instructions tell the respondent to consider a wide range of anxiety symptoms (e.g., panic attacks, worries, flashbacks) when answering the questions, and the time frame is “during the past week”. A psychometric analysis of the OASIS scale found good internal consistency (α = .80), test-retest reliability (k = .82) and convergent validity for this instrument. The Spanish version of the OASIS confirmed the factorial structure and reliability and validity data obtained by the original authors (internal consistency in both populations, general and clinical (α = .0.86 and test-retest reliability (k = .84) [94].

##### *Overall Depression Severity and Impairment Scale (ODSIS)* [92]

The ODSIS is a self-report measure with five items. Individuals select among five different response options ranging from 0 to 4 for each item. This scale evaluates experiences related to depression. The ODSIS measures the frequency and severity of depression, as well as the level of avoidance, work/academic/home interference, and social and everyday life impairment related to depression symptoms. The ODSIS can also be used to assess severity and impairment associated with low mood. In the Spanish version of the ODSIS, the internal consistency has been shown to be excellent, with a Cronbach’s alpha between .91 and .94 and good convergent and discriminant validity [95].

#### Expectation of treatment scale and opinion of treatment scale.

The Expectation of Treatment Scale and Opinion of Treatment Scale are questionnaires adapted from Borkovec and Nau [96]. Each scale contains five items, rated from 0 (“strongly disagree”) to 10 (“strongly agree”), which cover how logical the treatment seemed, to what extent it could satisfy the patient, whether it could be used to treat other psychological problems, and its usefulness for the patient’s specific problem. The expectation scale is applied once the intervention has been explained, at the end of the “Welcome module”. This scale measures the patient’s subjective expectations about the treatment. In addition, the opinion scale is administered when the patient has completed the treatment, and its aim is to assess satisfaction with the intervention. Our group has used this questionnaire in several research studies [48, 97].

The study measures and assessment times are summarized in Table 2.

**Table 2 Tab2:** Study measures and assessment times

Measure	Aim	Time of assessment
MINI Neuropsychiatric Interview	Diagnosis	BL, Post-T and FU
PANAS	Positive and negative affect	Post-T and Post-module
BDI-II	Severity of depression	BL, Post-T and FU
BAI	Severity of anxiety	BL, Post-T and FU
OCI-R	Severity of OCD symptoms	BL, Post-T and FU
PDSS-SR	Severity of PD and agoraphobia symptoms	BL, Post-T and FU
PSWQ	Severity of GAD symptoms	BL, Post-T and FU
SIAS	Severity of SAD symptoms	BL, Post-T and FU
NEO FFI	Neuroticism and Extraversion	BL, Post-T and FU
EQ-5D	Health-related quality of life	BL, Post-T and FU
OASIS	Severity of anxiety	Post-module
ODSIS	Severity of depression	Post-module
Suicide item	Suicidal ideation	BL, Post-module, Post-T and FU
Expectation of Treatment Scale	Expectation of treatment	BL
Opinion of Treatment Scale	Opinion of treatment	Post-T

*BL*, Baseline; *Post-T*, post-treatment; *FU*, follow-ups, 3 and 12-month follow-ups; *PANAS*, Positive and Negative Affect Scale; *BDI-II*, Beck Depression Inventory-II; *BAI*, Beck Anxiety Inventory; *OCI-R*, Obsessive-Compulsive Inventory-Revised; *PDSS-SR*, Self-Reported Panic Disorder Severity Scale; *PSWQ*, Penn State Worry Questionnaire; *SIAS*, Social Interaction Anxiety Scale; *NEO FFI*, NEO-Five Factor Inventory; *EQ-5D*, EuroQoL-5D questionnaire; *OASIS*, Overall Anxiety Severity and Impairment Scale; *ODSIS*, Overall Depression Severity and Impairment Scale

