**Methods:**

The study is a randomized controlled trial. 207 participants will be randomly assigned to: a)*Transdiagnostic Internet-based protocol (TIBP),* b)*Transdiagnostic Internet-based protocol + positive affect component (TIBP + PA),* or c)a Waiting List control group (WL). Primary outcomes measures will be the BDI-II, the BAI, and the PANAS. Secondary outcomes will include diagnosis-specific measures of the principal disorder. Participants’ treatment acceptance will also be measured. Participants will be assessed at pre-, post-treatment, and 3- and 12- month follow-ups. The data will be analyzed based on the Intention-to-treat principle. Per protocol analyses will also be performed.

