## Methods/Design

### Study design

A three-armed randomized controlled trial (RCT) will be conducted. Participants will be randomly allocated to one of three conditions: a) *Transdiagnostic Internet-based protocol (TIBP)*, b) *Transdiagnostic Internet-based Protocol + Positive Affect component (TIBP + PA),* and c) *Waiting List control condition (WL)*. For ethical reasons, participants in the control condition will be offered the possibility of receiving the treatment protocol. Block randomization will be performed within each stratum in order to ensure that all primary diagnoses are equally represented across conditions. Measures will be taken at post-randomization, after the treatment, and at 3- and 12-month follow-ups, in order to test whether the improvements achieved during the therapy are maintained in the long term.The study flowchart is shown in Fig. 1. The study will be conducted following the CONSORT statement (Consolidated Standards of Reporting Trials, http://www.consort-statement.org) [57, 58] the CONSORT-EHEALTH guidelines [59], and the SPIRIT guidelines (Standard Protocol Items: Recommendations for Interventional Trials) [60, 61].

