### Data analyses

Intention-to -treat analyses and per protocol analyses will be performed, and CONSORT recommendations will be followed [98]. First, the three groups will be compared to verify that there are no significant differences among them at baseline on the outcome measures in order to confirm that they are comparable after randomization. One-way ANOVAs for continuous variables and Chi-squared tests of independence for categorical ones will be used. For the continuous outcome measures on the posttest, the homoscedasticity assumption will be assessed with the Levene test. Where this assumption is met, the usual *F*-test will be applied to compare the posttest means for the three experimental conditions. If the homoscedasticity assumption is not met, the Brown-Forsythe *F*-test will be applied. Statistically significant *F*-tests will be followed by post hoc comparisons. In particular, the Tukey procedure will be applied where the homoscedasticity assumption is met, and the Games-Howell procedure if this assumption is not met.

The intention-to-treat principle will be used when analyzing primary and secondary post-treatment data and data collected at the 3- and 12-month follow-ups, using mixed-effect models with full information maximum likelihood estimation. This method has been recommended due to its flexibility on repeated-measures ANOVAs in handling missing data more appropriately [99]. To complement the results of the ANOVAs and post hoc comparisons, effect sizes will be calculated by using the standardized mean difference proposed by Cohen [62]. These effect sizes will be calculated to assess both within- and between-group changes, all of them based on a pooled standard deviation.

Although per protocol analyses (completers only analysis) suffer from selection bias, they will also be conducted to help to draw conclusions about the maximum treatment efficacy in patients who comply fully with the treatment [100].

When the trial ends, the analytic methodology for the RCT will be reviewed before analyzing the data in order to select the most appropriate analytic procedures.

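### Table 2 gives the PANAS, a primary outcome, no baseline and no follow-up assessment, which contradicts the abstract, the study design and the planned analyses

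*Protocol article*

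**What the plan says.** The abstract of the protocol article states: "Primary outcomes measures will be the BDI-II, the BAI, and the PANAS". It gives one set of time points for the trial: "Participants will be assessed at pre-, post-treatment, and 3- and 12- month follow-ups". The Study design section agrees: "Measures will be taken at post-randomization, after the treatment, and at 3- and 12-month follow-ups".

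Table 2 (Study measures and assessment times) lists the PANAS at "Post-T and Post-module". BDI-II and BAI are listed at "BL, Post-T and FU", as are secondary measures such as the NEO FFI and the EQ-5D. The table's footnote explains FU as "follow-ups, 3 and 12-month follow-ups".

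The Data analyses section first sets out to verify that "there are no significant differences among them at baseline on the outcome measures". It then plans mixed-effect models for primary and secondary outcomes at post-treatment and both follow-ups, and effect sizes for change within and between groups.

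The section Adaptation to the web says that unnamed initial online questionnaires form the pre-treatment assessment. It names the PANAS only in connection with the modules: "post-module brief questionnaires to evaluate anxiety, depression, and positive/negative affect (OASIS, ODSIS, PANAS) are also filled out throughout the program".

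**The concern.** A primary outcome has two incompatible schedules in one document. The general text implies four assessments; the only schedule that names the PANAS gives post-treatment plus post-module scores. No part of the text names the PANAS at baseline or at follow-up.

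Positive affect is what the added component targets, and hypothesis (c) is that TIBP + PA outperforms TIBP on positive-affect measures. If the online batteries were built from Table 2, the trial would have no pre-treatment PANAS score and no evidence on whether a gain in positive affect lasts. A baseline score that was not collected cannot be obtained once a participant has started treatment.

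**Working it through.** **1. The planned PANAS analyses against the Table 2 schedule.**

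| Planned use (Data analyses) | PANAS data needed | Available under Table 2? |
|---|---|---|
| Baseline comparison of the three arms | Baseline, all arms | No |
| F-test on posttest means, then Tukey or Games-Howell | Post-treatment, all arms | Yes |
| Within-group effect sizes, pre to post | Baseline and post-treatment | No |
| Mixed models, post-treatment part | Post-treatment | Yes |
| Mixed models, follow-up part | 3 and 12 months | No |

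**2. Whether post-module scores fill the gap.** They are completed inside the program, so the first one follows module 1, after treatment content has begun. Waiting-list participants are offered the intervention only after the waiting time (Ethics section), so they have no post-module scores while they wait. PANAS values before or during the comparison period, other than post-treatment, are therefore:
- waiting list: none;
- TIBP and TIBP + PA: post-module scores only, all after the start of treatment.

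**3. Whether the table's format explains the row.** It does not. The suicide item's row combines baseline, post-module, post-treatment and follow-up, so the table can show a mixed schedule.

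**4. Whether any stated figure depends on the missing assessments.** The Sample size section assumes a one-way ANOVA with three groups, f = 0.25, alpha .05 and power .80. With noncentrality λ = f² × N:
- N = 159 gives λ = 0.0625 × 159 = 9.94 and power 0.805. The smallest N reaching .80 is 158, so 159 with equal groups reproduces the plan's figure.
- 159 × 1.3 = 206.7, which gives the stated 207.

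This calculation compares posttest means and uses no baseline score. Adding a baseline PANAS changes neither number.

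**5. Illustration only: what a baseline could add if it were used as a covariate.** Two groups of 53 (TIBP + PA against TIBP), d = 0.5, two-sided .05.
- Without a baseline: noncentrality d × √(n/2) = 0.5 × √26.5 = 2.57 on 104 df; power 0.72.
- With a baseline at correlation r, replace d by d/√(1 − r²):

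| Assumed r | Adjusted d | Power |
|---|---|---|
| 0.3 | 0.524 | 0.76 |
| 0.5 | 0.577 | 0.84 |
| 0.7 | 0.700 | 0.95 |

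The document gives no correlation and specifies no baseline-adjusted model, so these values show a possible benefit and not a loss caused by Table 2.

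**The case against.** The strongest reply is that this is a slip in one table row. The abstract, the Study design section and the Data analyses section all point towards collection at baseline and follow-up, and the unnamed initial online questionnaires may well include the PANAS. Table 2 also looks incomplete elsewhere: the suicide item sits within the ODSIS and is listed at baseline, while the ODSIS row is post-module only. A slip is plausible, so it cannot be concluded that the data are lost. The contradiction still stands, because the only schedule that names this primary outcome disagrees with the rest of the text.

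Four stronger readings might be inferred, and the document does not support them:
- *Hypothesis (c) cannot be tested.* It names no time point, and a posttest comparison of randomized arms is valid without a baseline.
- *The PANAS is the only basis for hypothesis (c).* The hypothesis refers to positive-affect measures in the plural. The Discussion links positive affect to extraversion, which the NEO FFI measures at baseline, post-treatment and follow-up. The PANAS is nevertheless the only primary outcome that measures positive affect.
- *The trial loses power.* Under the stated posttest ANOVA, a baseline PANAS changes power by nothing.
- *No within-group change can be computed at all.* The active arms have scores after each module, including scores before the positive-affect modules. These allow change during treatment to be described, but not change from a pre-treatment state, and the waiting list has nothing comparable.

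The maintenance hypothesis (b) names only depressive and anxious symptoms. The missing PANAS follow-up therefore conflicts with the abstract, the Study design section and the Data analyses section, and not with that hypothesis.

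**Conclusion.** The point holds as an internal contradiction about a primary outcome. Under Table 2 as written, three planned PANAS analyses cannot be done: the baseline comparison, pre-post change from a true baseline, and the 3- and 12-month models. The posttest comparison remains valid, and the figures of 159 and 207 are unaffected.

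The contradiction rests on the text alone. The consequence assumes that data collection follows Table 2 and that the waiting list completes no modules during the waiting period. If the online batteries already include the PANAS at baseline and follow-up, only the table is wrong. If they do not, the loss is permanent for every participant already started, so the check should come before anything else.

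**What to change.** - Confirm that the online baseline and follow-up batteries contain the PANAS.
- Change the PANAS row of Table 2 to baseline, post-module (active arms), post-treatment and follow-up. The baseline, post-treatment and follow-up points should apply in all three arms on the same terms as BDI-II and BAI.
- If the baseline or follow-up PANAS was omitted deliberately, say so, and remove the PANAS from the baseline comparison, the pre-post effect sizes and the follow-up models.

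The cost is one corrected table row and, if the scale is missing, 20 items added to online assessments that already take place. The sample size does not change.
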